### Baseline characteristics

Baseline measurements will be recorded prior to randomization. Participant characteristics, including age, sex, height (cm), weight (kg), ethnicity, language, type of residence, and education level, will be collected. Caregiver information will also be recorded, including the caregiver's relationship to the participant and caregiver age. All outcome data collection points throughout the study timeline are presented in Table 1.

**Table 1 T1:** Data collection components and collection timeline.

**Construct**	**Outcome measure**	**Group**	**Baseline (T0)**	**8 weeks (T1)**	**6 months (T2)**	**12 months (T3)**
Socio-demographics		All participants	√	–	–	–
Health-related QoL	PedsQL 4.0	DS participants	√	√ (I+C)	√	√
		University students	√	√ (I+C)	√	√
Mental wellbeing	EPOCH	University students	√	√ (I+C)	√	√
Global perceived effect	GPE	DS caregivers	–	√ (I+C)	√	√
Friendship quality	FQQ	Intervention dyads only	–	√ (I)	√	√

DS, Young people with Down syndrome; I, Intervention group; C, Control group; PEDSQL 4.0, Pediatric Quality of Life Inventory version 4.0; EPOCH, Engagement, Perseverance, Optimism, Connectedness, and Happiness; GPE, The Global Perceived Effects scale; FQQ, Friendship Quality Questionnaire.

#### Health-related quality of life

Health-related quality of life for young people with DS will be measured using the PedsQL 4.0. The Pediatric Quality of Life Inventory (PedsQL) is a widely used tool to assess quality of life in children and adolescents aged 2–18 years with acute or chronic health conditions, including DS (20). For participants over 18 years old, the adult version of the PedsQL will be used where appropriate, or caregiver proxy reports will be obtained. The PedsQL 4.0 covers domains of physical functioning, emotional wellbeing, social interaction, and school functioning, and also provides a total score. Higher scores indicate better quality of life. This instrument has demonstrated good psychometric properties in young people, with internal consistency (Cronbach's α) ranging from 0.66 to 0.93 (21).

Caregivers of participants with DS will complete the GPE scale for QOL at T1 to provide an external assessment of change in the child's QOL. For analysis, responses of “very much improved” or “much improved” will be categorized as a clinically important improvement, while responses of “a little improved,” “no change,” or “worse” will be considered as no substantial improvement (22). GPE responses will be analyzed as an ordinal scale, with “worse” reported separately to assess potential deterioration.

#### Mental wellbeing

The EPOCH Measure of Adolescent Wellbeing is a scale used to assess positive psychological traits in young people (23). It consists of five dimensions: Engagement, Perseverance, Optimism, Connectedness, and Happiness. The EPOCH includes 20 items (4 per dimension) and was developed as a brief measure of positive youth psychological traits that may promote wellbeing and physical health (24).

#### Friendship quality

Friendship quality will be assessed using the Friendship Quality Questionnaire (FQQ), which measures key dimensions of peer friendship (such as companionship, conflict, help/support, security, and closeness) (25). The FQQ will quantify each participant's perception of their friendship, providing insight into the social relationship formed through the intervention.

### Adverse events

Any adverse events in either group will be documented using case report forms, including monitoring for social or emotional distress, with caregiver involvement as needed. The trial coordinator will maintain regular contact with participants (or parents/guardians of participants with DS) to monitor for any issues or adverse effects throughout the study.

### Statistical analysis

A target sample size of 12 dyads (12 per group) was selected to provide preliminary estimates of variability and feasibility, consistent with recommendations for pilot trials (26, 27), while remaining pragmatic given resource constraints in DS population studies. Statistical analysis will be performed by a researcher blinded to group allocation, and an independent statistician will verify the primary outcome analysis. The primary analysis will compare the shared book reading intervention group and the waitlist control group for the primary outcome at 8 weeks post-randomization. Secondary analysis will include analysis of secondary outcomes at 8 weeks post-randomization. Additionally, we will use an actor–partner interdependence model (APIM) to explore within-dyad relationships (examining how one member's baseline quality of life or mental wellbeing might influence both their own and their partner's outcomes). Dyad composition and potential differences in interpersonal dynamics will be accounted for within the APIM. For outcome comparisons, we will use mixed-effects linear models to account for repeated measures and dyad clustering, and results will be presented as mean differences between groups with 95% confidence intervals. Models will adjust for baseline scores in outcomes and covariates, including age, sex, and education level.

The primary analysis will be conducted using an intention-to-treat (ITT) approach. Secondary analyses will be performed after imputation of missing data. A sensitivity analysis will be conducted using multiple imputations for missing data (including all secondary outcomes and covariates in the imputation model). All analyses will be performed using R in RStudio (28).

Feasibility of the RCT will be evaluated based on participant adherence to the intervention and completion rates of outcome measures at each time point. Acceptability of the intervention will be assessed through qualitative feedback from participants in the intervention arm. Caregiver presence and group size will be documented and analyzed as potential moderators of intervention effects. We will maintain continuous consultation with the PPI panel throughout the study to gain insights into intervention implementation. This ongoing feedback will help researchers understand factors that encourage or discourage participation, improving study processes for consideration in future studies. We will also involve the PPI panel in disseminating findings, incorporating their input when presenting results to local stakeholders.

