### Study design

This study will be a pilot pragmatic parallel-group dyadic randomized controlled trial (RCT) comparing a shared book reading intervention (young people with DS paired with university student partners) to a minimal-activity control group.

All individuals with DS recruited into the study will be randomly paired with a university student to form a dyad. Depending on recruitment numbers, if more university students are enrolled than young people with DS, some dyads may consist of one participant with DS and two students (i.e., a 1:2 pairing). Each dyad will be randomized 1:1 to either the intervention group or the control group. Recruitment will take place over a 12-month period, with each participant involved in their assigned condition for 8 weeks. After this period, participants in the control group will also be offered the intervention. The primary outcome will be assessed at 8 weeks post- randomization. An extended phase will allow for exploration of long-term effects and sustainability, with outcomes measured at 6 and 12 months to inform future trial design.

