### Randomization and allocation

Participants within their dyads will be randomized (1:1) to either the intervention or control group. A computer-generated randomization list (using random block sizes of 2 and 4) will be prepared at the University of Macau, and allocation will occur after baseline data collection. An external statistician not involved in the study will perform the allocation centrally using this list. Researchers conducting the baseline and follow-up assessments will be blinded to group allocation.

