### Outcome measures

Outcome measures will be collected at baseline (T0) and 8 weeks post-randomization (T1) for both the intervention and control groups. Following the initial 8-week RCT phase, all participants (including those from the waitlist control group) will receive the intervention; additional follow-ups will be conducted at 6 months (T2) and 12 months (T3) post-randomization in this single-arm extension phase. For the intervention group, outcomes for participants with DS will be collected at the end of the final session through researcher-administered interviews. For the control group, 8-week outcomes for participants with DS will be collected via researcher-conducted telephone interviews. University student participants in both groups will complete their outcome measures through an online survey, with reminder prompts sent after 1 and 2 days if not completed.

At T1, dyads in the intervention group will complete one additional measure (assessing the dyad's overall friendship) that will not be administered to the waitlist control group; all other outcome measurements are identical for both groups. The primary outcome of this study is the health-related quality of life of young people with DS at 8 weeks (T1), measured using the Pediatric Quality of Life Inventory (PedsQL)4.0. Secondary outcomes include the mental wellbeing of the student partners (assessed using the EPOCH scale) and the quality of the friendship within the dyad (assessed via the Friendship Quality Questionnaire, FQQ). Additionally, caregivers of participants with DS will complete a Global Perceived Effect (GPE) scale to evaluate their perception of change in the quality of life of the participant with DS.

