### Addressing gaps in literature

Recent research suggests that interventions aiming to develop language skills in people with DS can indeed improve communication (29). Such interventions can take many forms, including incorporating books and magazines into regular activities and providing adequate guided practice (30). Previous meta-analyses have shown that language interventions, like shared book reading, can improve spoken language ability in children with neurodevelopmental disorders (31). Interventions included in these meta-analyses used various techniques, including shared reading, general language stimulation, direct language instruction, play-based language interventions, multimedia-assisted interventions, social interaction-based interventions, and family-involved interventions. Meta-regression indicated that longer sessions over extended periods were more beneficial than shorter, short-term interventions. This finding informed our decision to implement relatively longer sessions over an 8-week period in our trial, with the expectation that a sustained intervention could lead to larger effect sizes. Although our pilot is not fully powered to detect statistically significant differences, it will provide effect size estimates to inform the sample size of a future definitive RCT.

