However, several limitations should be acknowledged. First, the use of a waitlist control design, rather than an active concurrent control, may introduce potential bias, as control group participants will eventually receive the intervention. This design also raises the possibility of contamination, as control group participants may have access to books and opportunities to engage in shared reading with others outside the study. Second, blinding of participants to their group allocation (intervention or control) is not feasible, which may lead to differing expectations of improvement and influence outcomes during data collection. Finally, challenges related to recruitment and participant retention are anticipated, which could impact the study's overall feasibility and generalizability. As a pilot study, the sample size is limited, and the study may be underpowered to detect modest intervention effects. Consequently, any outcome differences will be interpreted cautiously and primarily used to inform the design of a larger trial. Despite these limitations, this pilot study represents an important first step in evaluating an innovative intervention. The insights gained will be invaluable for planning a definitive trial and could open new avenues for mental wellbeing promotion in young people with developmental disabilities (36).

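### The target of 12 dyads contradicts 12 per group under 1:1 randomization of dyads, so the primary-outcome n per arm could be 6 or 12

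*Protocol article*

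**What the plan says.** The target size is in the first sentence of Statistical analysis: "A target sample size of 12 dyads (12 per group) was selected to provide preliminary estimates of variability and feasibility". The unit of the second 12 is not given.

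Four other statements bear on how to read it:

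- Study design: "Each dyad will be randomized 1:1 to either the intervention group or the control group".
- Randomization and allocation: "Participants within their dyads will be randomized (1:1) to either the intervention or control group".
- Study design, on pairings if more students than young people with DS enrol: "some dyads may consist of one participant with DS and two students (i.e., a 1:2 pairing").
- Outcome measures: "The primary outcome of this study is the health-related quality of life of young people with DS at 8 weeks (T1"). Each dyad contains one young person with DS, so the number per arm for the primary outcome equals the number of dyads per arm.

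The article reports group comparisons as mean differences with 95% confidence intervals (Statistical analysis). In the Discussion (Addressing gaps in literature) it says of the pilot that "it will provide effect size estimates to inform the sample size of a future definitive RCT".

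**The concern.** The sentence names one unit, the dyad, and gives 12 both as the total and as the per-group number. With two groups and 1:1 allocation of dyads, both cannot be true in that unit.

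At stake is the number of young people with DS in each arm for the primary outcome, which is 6 or 12. The size is justified as giving preliminary estimates of variability and feasibility, and how well variability can be estimated depends directly on this number. The planned adjustment for baseline score, age, sex and education level is also a much heavier load on 12 young people with DS than on 24. A reader of the eventual report could not tell whether the trial met its target.

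**Working it through.** **1. The plan's own figure.** Inputs: 12 dyads and 12 per group (Statistical analysis); two groups, 1:1, dyad as unit (Study design; Randomization and allocation).

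- 12 dyads ÷ 2 groups = 6 dyads per group, not 12.
- 12 dyads per group × 2 groups = 24 dyads, not 12.
- Counting people: 12 dyads × 2 people = 24 people, and 24 ÷ 2 = 12 people per group. This agrees, but only if the unit changes inside the sentence and every dyad is one-to-one. Each 1:2 pairing adds a person and breaks the count.

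The figure is not reproduced in dyads. It is reproduced in people, with 6 young people with DS per arm.

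**2. Precision of the 8-week mean difference, in SD units.** The article gives no SD, effect size, baseline correlation or dropout rate. The correlation ρ below is therefore an assumption, and no dropout is assumed.

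Half-width = t(0.975, df) × √(1 − ρ²) × √(2/n), with df = 2n − 2 unadjusted and one fewer when baseline is included.

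- n = 6, unadjusted: 2.228 × 0.577 = 1.29
- n = 12, unadjusted: 2.074 × 0.408 = 0.85

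| Analysis | 6 per arm | 12 per arm |
|---|---|---|
| Unadjusted | ±1.29 | ±0.85 |
| Baseline-adjusted, ρ = 0.5 | ±1.13 | ±0.74 |
| Baseline-adjusted, ρ = 0.7 | ±0.93 | ±0.61 |
| ρ = 0.5, four covariates at one df each | ±1.22 (6 df) | ±0.74 (18 df) |

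Unadjusted, the interval at 6 per arm is about 1.5 times as wide (1.29 ÷ 0.85).

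**3. Precision of the SD.** The 95% limits, as multiples of the estimate, are √(df/χ²(0.975, df)) and √(df/χ²(0.025, df)).

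- 6 per arm (10 df): 0.70 to 1.75
- 12 per arm (22 df): 0.77 to 1.42

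**4. The effect estimate as an input to a later trial (secondary).** If the observed standardized difference were 0.5, its exact 95% interval would be −0.66 to 1.64 at 6 per arm and −0.32 to 1.31 at 12.

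Now assume a true difference of 0.5, 80% power and two-sided 5%. The definitive trial then needs about 63 per arm. In 200,000 simulated pilots, a size taken straight from the observed effect fell within a factor of two of 63 in 23% (6 per arm) or 33% (12 per arm). The observed effect had the wrong sign in 19% or 11%.

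**The case against.** The strongest defence is that the bracket counts people. Twelve one-to-one dyads are 24 people, 12 in each group. The 1:2 pairing is only a contingency on recruitment, so it need not disturb a target. This is a fair reading, and it means that the defect may be an unlabelled unit and not a doubled trial. It does not settle the matter: the text does not say so, and the primary-outcome n per arm would then be 6, a number the article never states.

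A reader might infer more than the documents support:

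- **That the intended size is 24 dyads.** This is one candidate. Nothing in the text chooses between it and 12. The flow diagram (Figure 1) was not visible in the text reviewed and may carry numbers.
- **That the claimed agreement with pilot-trial recommendations is wrong.** The cited sources are not available here, so whether 6 per group departs from them cannot be judged.
- **That the end of recruitment is undefined.** Study design also bounds recruitment by a 12-month period.
- **That the Discussion commits to powering the definitive trial on the observed effect.** It says the estimates will inform that size. The article concedes limited power ("As a pilot study, the sample size is limited, and the study may be underpowered to detect modest intervention effects"), promises cautious interpretation, and plans confidence intervals. How the later trial is powered belongs to its own protocol.
- **That sizing from the pilot would favour over-optimistic effects.** That needs selection on a favourable result, and no such rule is planned. The imprecision in step 4 gives oversized as well as undersized trials.

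**Conclusion.** The contradiction stands and needs correcting. In the unit that the sentence names and the trial randomizes, 12 in total and 12 per group are incompatible, and the primary-outcome n per arm is left at either 6 or 12. Unadjusted, that is a half-width of about ±1.29 against ±0.85 SD; the SD's 95% interval is 0.70–1.75 against 0.77–1.42 times the estimate.

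The unadjusted widths and the SD limits follow from n alone under normality, equal variances and complete data. The adjusted widths rest on assumed baseline correlations, and the figures in step 4 on an assumed effect, power and significance level. Adjustment narrows the intervals but does not remove the gap between the two readings.

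The Discussion sentence on effect sizes is a secondary matter of wording. At either size the estimate is too imprecise to size a trial on its own, but the article does not say that it would be used alone.

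**What to change.** **Needed.** In Statistical analysis, state one total and one per-group number, both in dyads: either 24 dyads (12 per group) or 12 dyads (6 per group). The choice is the sponsor's. Say that the primary analysis has one young person with DS per dyad, and give the expected precision for the chosen size. Check that Figure 1 agrees.

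**Optional.** In Addressing gaps in literature, say that the pilot will mainly supply the SD, the baseline-to-8-week correlation and retention for planning, and that the effect will be reported with its confidence interval and not used alone to size the definitive trial.

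**Cost.** One sentence must change, and a second may. Correcting the text does not in itself require more participants. The downside is that the stated precision may look less favourable, particularly if 12 dyads is the total.

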### Shared book reading intervention

The shared book reading intervention will be led by an intervention leader, a doctoral research student who is a registered nurse. The intervention leader will be assisted by facilitators who will receive 1-h training in DS-adapted communication strategies (e.g., visual supports, paced questioning) and engagement techniques (e.g., dialogic reading, sensory accommodations). Sessions will comprise: (i) a 10-min icebreaker involving a musical chairs adaptation (flower-passing with music, followed by sharing a favorite word from previous sessions) and facial expression imitation games to build rapport; (ii) a 30-min shared reading using PPI-approved books, with adaptations for non-verbal participants (yes/no questions) and attention challenges (10-min reading blocks with stretch breaks); and (iii) a 10-min reflection using visual prompts (emoji cards for “favorite part” discussions) and icon-based logbook entries. This training will be delivered by the intervention leader. Weekly facilitator reports will document implementation challenges (e.g., participant disengagement) for iterative problem-solving.

Facilitators will maintain participant's engagement, and caregivers of young people with DS are welcome to attend. To minimize bias, facilitators will follow a standardized manual (Supplementary File 1: Intervention Facilitator Manual). Session fidelity across all dyads will be assessed using checklists (Supplementary File 2: Fidelity Checklist and Scoring Criteria) completed by the intervention leader. Each session will conclude with a brief reflection period during which participants discuss what they have read and plan for the next session. Weekly reminders will be sent to families and students regarding session times. Attendance will be incentivized through a sticker system, with participants collecting stickers in a provided scrapbook.

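### The outcome model has no term for shared reading sessions; if intervention dyads meet in groups, as the protocol implies, the 8-week confidence intervals are too narrow

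*Protocol article*

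**What the plan says.** The Statistical analysis section of the protocol article fixes the outcome model: "we will use mixed-effects linear models to account for repeated measures and dyad clustering, and results will be presented as mean differences between groups". On the fixed part it adds: "Models will adjust for baseline scores in outcomes and covariates, including age, sex, and education level". No session or reading-group term appears in either part.

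Randomization is by dyad: "Each dyad will be randomized 1:1 to either the intervention group or the control group" (Study design).

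Three statements bear on how the intervention is delivered:

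- Shared book reading intervention: "The shared book reading intervention will be led by an intervention leader, a doctoral research student who is a registered nurse". Facilitators, in the plural, assist.
- The same section says each session opens with "a 10-min icebreaker involving a musical chairs adaptation (flower-passing with music, followed by sharing a favorite word from previous sessions").
- Statistical analysis: "Caregiver presence and group size will be documented and analyzed as potential moderators of intervention effects".

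The Control group section says that control pairs are not introduced during the first 8 weeks. Control youth receive three books to read alone or with family.

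**The concern.** A flower-passing game with music makes little sense for a single pair, and a recorded group size suggests that sessions hold more than one dyad. If so, intervention dyads in the same session share facilitators, peers and occasion, and their outcomes are likely to be correlated. Controls share nothing comparable. That is a partially nested design: dyads are randomized individually, but clustering arises after randomization in one arm only.

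The stated model does not cover this correlation. For PedsQL in youth with Down syndrome the dyad term cannot absorb it, because each dyad contains only one such person. For EPOCH the dyad term covers two students attached to the same youth, but not students of different dyads who attend the same session. Treating group size as a moderator changes the modelled mean and leaves the correlation between dyads untouched.

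Two things are at stake: the width of the reported 8-week intervals, and the variability estimate that the pilot exists to supply to a definitive trial.

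**Working it through.** **The plan's own figure.** The sample size statement is "A target sample size of 12 dyads (12 per group) was selected to provide preliminary estimates of variability and feasibility". It rests on pilot-trial recommendations, with no power, effect size or SD, so there is nothing to reproduce. Its implied precision under independence, with SD 1, is t(0.975, 2n−2) × √(2/n). This is 0.85 SD at n = 12 per arm and 1.29 SD at n = 6 per arm. The wording can be read as 12 or 24 dyads in total, so both were run, with 12 per arm as the main case.

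**Inputs.**

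- From the protocol: 1:1 allocation by dyad, 12 per arm, a 95% interval (equivalent to a two-sided 5% test), no sessions in the control arm.
- Assumed, because not given: session-group ICC 0.05, 0.10 or 0.20; m dyads per group; equal total variance in both arms; true programme effect zero.

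**Variance of the arm difference.** With clustering in one arm only, true variance / independence variance = [1 + (m−1)ICC + 1] / 2.

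- m = 3: 1 + ICC, giving 1.05, 1.10, 1.20.
- m = 6: 1 + 2.5 × ICC, giving 1.125, 1.25, 1.50.
- m = 12: 1 + 5.5 × ICC, giving 1.275, 1.55, 2.10.

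The square roots give the true standard error over the independence standard error: 1.03 to 1.10, 1.06 to 1.22, and 1.13 to 1.45. As a share of the true variance (1 − 1/ratio), the shortfall is 5 to 17%, 11 to 33%, and 22 to 52%.

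**Error of the independence analysis.** Simulated t-test, 200,000 runs per setting, outcome SD 1, no baseline adjustment:

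| Per arm | Groups | ICC 0.05 | ICC 0.10 | ICC 0.20 |
|---|---|---|---|---|
| 12 | six of 2 | 5.3% | 5.5% | 6.3% |
| 12 | four of 3 | 5.6% | 6.2% | 7.5% |
| 12 | three of 4 | 5.9% | 6.9% | 8.7% |
| 12 | two of 6 | 6.6% | 8.1% | 11.4% |
| 12 | one of 12 | 8.3% | 11.9% | 19.0% |
| 6 | two of 3 | 5.6% | 6.2% | 7.5% |
| 6 | one of 6 | 6.4% | 8.0% | 11.5% |

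A second simulation used analysis of covariance on baseline (assumed baseline–outcome correlation 0.6, 10,000 runs). It gave nearly the same: 6.3, 7.9 and 11.0% for two groups of six, and 8.2, 11.3 and 17.6% for one group of 12.

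**Does a session-group term repair it?** The intervention variance was taken from the group means and the control variance from individuals, with Satterthwaite degrees of freedom, at 12 per arm and ICC 0.01 to 0.20.

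- Four groups of 3: error 4.9 to 5.1%; median half-width 0.88 to 0.97 SD, against about 0.83 under independence.
- Three groups of 4: error 5.2 to 5.7%; half-width 0.90 to 1.04 SD.
- Two groups of 6: error 6.2 to 7.8%, so not fully controlled; half-width 0.89 to 1.15 SD, against 0.83 to 0.81.
- One group of 12: the group variance cannot be estimated, so no model term helps.

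**The case against.** **Group delivery is inferred.** The Abstract describes the intervention as a weekly session pairing one young person with one student, and the reading itself is done in pairs. Group size is undefined and could mean the 1:1 versus 1:2 pairings allowed under Study design. The facilitator manual, which is not shown, may settle the format. A reader might take it as documented that the dyads read in groups; the text does not go that far. The inference is still strong. The icebreaker needs several people, facilitators are plural, and pairing structure is already handled elsewhere in the same section as dyad composition within the actor–partner model.

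**The largest figures need the least supported layout.** Recruitment runs over 12 months, with each participant in their condition for 8 weeks. Unless dyads start in batches, one stable group of 12 cannot form, and small or changing groups are more plausible. With groups of two or three the error is only about 5 to 7.5%. This stands, and it limits the size of the point.

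**No formal test is named.** No alpha is stated, and the protocol says the trial may be underpowered and that differences will be read cautiously. A reader might infer that the trial will wrongly declare a programme effect, or that the definitive trial will be undersized. Neither follows: no decision hangs on a test, and nothing says the later trial would ignore clustering. The interval and the variance estimate remain affected.

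**The random-effects list may not be exhaustive.** Detail of this kind is often left to an analysis plan. That softens the point, but the sentence does name its levels and omits this one.

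**Conclusion.** The point holds conditionally. If intervention dyads share sessions, as the protocol strongly implies, the stated model omits a level of clustering present in one arm only, and the 8-week intervals for PedsQL and EPOCH are too narrow for any positive session-group ICC.

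The size depends on two quantities the protocol does not give. At 12 dyads per arm and ICC 0.05 to 0.20, the variance of the arm difference is 1.05 to 1.20 times the independence value with groups of three, 1.125 to 1.50 times with groups of six, and 1.275 to 2.10 times with one group of 12. The first is minor, the second worth correcting, and the third serious but unlikely given the recruitment period. The calculations treat one continuous outcome per dyad. They were not run separately for EPOCH with two students in a dyad, so for EPOCH the direction carries over but the exact figures may not.

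The cautious reading promised for a pilot does not remove the issue, because estimating variability is the stated reason for the sample size. An effect of the single leader that is common to all groups cannot be separated from the programme by any model in this design.

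**What to change.** 1. State in the intervention section whether dyads meet in shared sessions, and define group size.
2. Record the session group attended by each intervention dyad. This may be impossible to rebuild reliably later.
3. In Statistical analysis, keep the dyad term and add a session-group random effect in the intervention arm only, with controls as singletons and Kenward–Roger or Satterthwaite degrees of freedom. The dyad term must stay, because 1:2 pairings put two students in one dyad.
4. If fewer than about four groups form, or membership changes so that the variance cannot be estimated, report the mean difference with intervals recalculated at fixed ICCs of 0, 0.05, 0.10 and 0.20 beside the unadjusted one. State that the unadjusted interval does not cover group-to-group or leader variation.
5. Carry the same ICC range into the definitive trial's sample size.

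The cost is one identifier per intervention dyad and revised wording; the intervention, recruitment and outcomes do not change. The statistical price is a wider interval. For two groups of six, the half-width rises from about 0.83 SD to as much as 1.15 SD at ICC 0.20. With few groups the between-group variance is assumed rather than estimated.
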